#### Conventional Treatment Group

##### Basic Medical Treatment

Standard pharmacological management will follow the 2024 Chinese guidelines, including risk factor control. Medication type and dose will be individualized based on comorbidities and physician judgment, but treatment categories, target parameters (blood pressure of <140/90 mm Hg and low-density lipoprotein cholesterol level of <2.6 mmol/L), and monitoring schedules will be uniform across participants.

##### Basic Rehabilitation Therapy

A standardized rehabilitation framework will be applied, consisting of three core modules:

Exercise therapy: 30 minutes per session, 5 sessions per week, including balance training, gait training, and limb mobility exercises. Intensity will be tailored to baseline motor ability using the Fugl-Meyer Assessment, but progression will follow a predefined stepwise protocol.Occupational therapy: 30 minutes per session, 5 sessions per week focusing on activities of daily living such as dressing, feeding, and household tasks using standardized task sequences.Physical agent modality therapy: where indicated, treatments such as transcranial direct current stimulation or low-frequency pulsed magnetic therapy will be applied following fixed device settings and session lengths.

##### Cognitive Function Training

Structured cognitive training will target attention, memory, judgment, reasoning, and executive function. Each session will last 30 minutes once daily, 5 days per week for 8 weeks, delivered using a standardized digital training program and exercise booklet. Therapists will follow a fixed progression schedule, with difficulty levels increasing every 2 weeks.

##### Sham Acupuncture Procedure

Sham acupuncture will be administered at nonacupoint sites approximately 2 cm posterior to Baihui (GV20), 1.5 cm lateral to Shenting (GV24), and 2 cm adjacent to Sishencong (EX-HN1), avoiding recognized meridians [40]. A nonpenetrating placebo needle will provide superficial tactile pressure without skin penetration, mimicking real acupuncture sensation but avoiding physiological effects [41]. Sessions will last 20 minutes once daily, 5 days per week for 8 weeks.

#### Acupuncture Treatment Group

##### Overview

Participants will receive all the aforementioned conventional therapy components and real acupuncture in place of sham acupuncture. Selected acupoints will include GV20, GV24, and EX-HN1. Disposable sterile filiform needles will be inserted to a depth of 10 to 15 mm and manipulated to elicit *deqi* sensation. Each session will last 20 minutes once daily, 5 days per week for 8 weeks.

##### Standardization and Quality Control

All therapists and acupuncturists will undergo a 2-day training workshop on the standardized protocol. Detailed treatment manuals and checklists will be used to guide therapy delivery. Treatment logs will be completed after every session, documenting date, time, duration, completion status, and any deviations from the protocol. Monthly audits will be conducted by the project manager to ensure adherence to the protocol.

### Primary Outcomes

All practitioners involved in the study are experienced and professionally trained rehabilitation physicians or therapists. The MoCA will serve as the primary outcome measure for statistical inference as it is more sensitive to detecting MCI and changes in executive and visuospatial domains commonly observed after stroke. The MMSE will be analyzed as a key secondary outcome to provide complementary information and enable comparison with previous literature where the MMSE was the predominant tool.

Both assessments will be administered by the same trained therapist before and after the intervention to ensure consistency and minimize interrater variability. The MoCA evaluates a broad range of cognitive domains, including visuospatial and executive abilities, naming, memory, attention, language, abstraction, delayed recall, and orientation. It consists of 12 subitems, with a total score of 30 points; a score of >26 is generally considered healthy. For participants with <12 years of education, 1 point will be added to the total score to adjust for education bias.

The MMSE also provides a total score of 30 points and assesses domains such as orientation, registration, attention and calculation, recall, language, and praxis. While the MMSE is widely used in clinical settings for its brevity and utility in detecting moderate to severe cognitive impairment, the MoCA is more sensitive to subtle cognitive changes, making it more suitable as the primary statistical end point in this trial.

Multiple comparisons will be addressed by applying Bonferroni or other appropriate correction methods for secondary outcomes, ensuring statistical rigor while capturing a comprehensive and nuanced picture of cognitive changes following acupuncture intervention. The timing of treatment assessments and data collection are shown in Table 1.

**Table 1 table1:** Timing of treatment assessments and data collection.

Item			Study period				
			Before enrollment (−1 wk)	Baseline (0 wk)	Intervention period		
					4 wk		8 wk
Inclusion criteria			✓				
Exclusion criteria			✓				
Informed consent			✓				
Randomization				✓			
Allocation				✓			
**Interventions**							
	Acupuncture treatment group				✓	✓	
	Sham acupuncture group				✓	✓	
**Assessments**							
	MMSE^a^			✓	✓	✓	
	MoCA^b^			✓	✓	✓	
	MBI^c^			✓	✓	✓	
	MOS SF-36^d^			✓	✓	✓	
	Routine MRI^e^ scanning			✓	✓	✓	
	Resting-state fMRI^f^			✓	✓	✓	
	DTI^g^			✓	✓	✓	

^a^MMSE: Mini-Mental State Examination.

^b^MoCA: Montreal Cognitive Assessment.

^c^MBI: modified Barthel index.

^d^MOS SF-36: Medical Outcomes Study 36-Item Short-Form Health Survey.

^e^MRI: magnetic resonance imaging.

^f^fMRI: functional MRI.

^g^DTI: diffusion tensor imaging.

### Secondary Outcomes

#### Ability to Perform Activities of Daily Living

The modified Barthel index will be used for pre- and posttreatment assessments. Scoring is as follows: 100 points indicate normal ability to manage daily-life activities; scores of >60 imply mild dysfunction and mild life dependence, scores of 41 to 59 indicate moderate dysfunction and moderate life dependence, scores of 21 to 40 reflect severe dysfunction with evident life dependence, and scores of <20 denote total life dependency.

#### Quality of Life

The Medical Outcomes Study 36-Item Short-Form Health Survey will be used for evaluation before and after treatment. This comprehensive scale covers 8 domains, encompassing physical functioning, role limitations due to physical health problems, bodily pain, general health perceptions, vitality, social functioning, role limitations due to emotional problems, and mental health.

#### fMRI Scanning Scheme

A Siemens MAGNETOM Trio 3.0T magnetic resonance imager will be used for routine MRI scanning, resting-state fMRI, and diffusion tensor imaging (DTI) data collection. Both pre- and posttreatment scans will be conducted using this state-of-the-art imaging technology. For imaging data, false discovery rate correction will be used.

Conventional MRI scan sequence and parameters are as follows: (1) repetition time (TR)=600 ms, echo time (TE)=10 ms, layer thickness=5 mm, field of view (FOV)=240 mm, and matrix size=256 × 256 (T1-weighted image parameters); (2) TR=3000 ms, TE=113 ms, layer thickness=5 mm, FOV=240 mm, and matrix size=256 × 256 (T2-weighted image parameters); and (3) TR=8800 ms, TE=79 ms, layer thickness=5 mm, FOV=240 mm, and matrix size=256 × 256 (T2-weighted fluid-attenuated inversion recovery parameters).

The scanning sequence and parameters for fMRI are as follows. First, the anatomical data are collected via a T1-weighted 3D spoiled gradient–recalled sequence, and the volume images are obtained. The scanning parameters are TR=1900 ms, TE=2.26 ms, layer thickness=1 mm, FOV=250 mm, and matrix size=256 × 256. Second, the resting fMRI data are collected via real-time imaging processing. Gradient-recalled echo-planar imaging recalls the image with the following parameters: TR=2000 ms, TE=30 ms, continuous scanning of 30 layers, layer thickness=4 mm, FOV=200 mm, matrix size=64 × 64, and scanning time of approximately 8 minutes and 6 seconds.

The scanning sequence and parameters for DTI are as follows. First, the anatomical data are collected via a T1-weighted 3D spoiled gradient–recalled sequence, and the volume images are obtained. The scanning parameters are TR=1900 ms, TE=2.26 ms, layer thickness=1 mm, FOV=250 mm, and matrix size=256 × 256. Second, the DTI data are scanned through an echo-planar imaging sequence in the horizontal axis. The following parameters**―**TR=7200 ms, TE=104 ms, 49 layers, 2.5-mm thickness, number of excitations once, matrix size=128 × 128, FOV=240 × 240 mm, and 64 nonlinear diffusion gradients (b=0.1000 seconds per mm^2^)**―**are applied. The scanning duration is approximately 8 minutes and 11 seconds.

### Safety Measurements

Acupuncture typically does not lead to severe adverse events [42,43]. However, given the neurological population and the invasive nature of acupuncture, a formal data safety monitoring plan will be implemented. An independent data safety monitoring board (DSMB), comprising a neurologist, an experienced acupuncturist not involved in the trial, and a biostatistician, will oversee participant safety throughout the study. The DSMB will review cumulative safety data and adjudicate all adverse events and serious adverse events independently of the trial investigators, including assessment of causality, severity, and relatedness to the intervention.

All unexpected adverse events will be promptly reported by clinical staff to the investigator or project manager and documented in detail. These reports will be forwarded to the DSMB for independent review within 72 hours. Should a serious adverse event occur, the principal investigator and ethics committee will be notified immediately, and the DSMB will make recommendations on whether the participant should be withdrawn from the trial or whether trial procedures require modification. The DSMB will meet quarterly or more frequently if safety concerns arise to ensure continuous monitoring of participant well-being and trial integrity.

### Data Management

During participant recruitment, screeners will gather demographic and baseline characteristic data. The final assessor will measure primary and secondary outcomes at baseline and at the conclusion of the 8-week intervention. A research assistant will oversee quality control during data collection and take charge of data entry. The project manager will assume responsibility for the initial data cleaning, identification, encoding, and transformation into the suitable format for subsequent data analysis. All study data will be entered into an electronic database with range and consistency checks. Data access will be restricted to authorized study staff. Missing data will be minimized through real-time monitoring and reminders. If outcome data are missing, multiple imputation by chained equations will be applied under the assumption of being missing at random. Pooled estimates across imputations will be reported, with sensitivity analyses using complete-case data.

### General Data and Efficacy Indicator Statistical Analysis

All statistical analyses will be conducted in SPSS (version 20.0; IBM Corp), with the significance level set at *P*<.05. Analyses will be divided into two categories: (1) general data and efficacy indicators and (2) fMRI data processing and statistical analysis. For general data and efficacy indicators, two-tailed independent sample *t* tests or chi-square tests will be used to assess pre- and posttreatment differences in overall cognitive function, activities of daily living, and quality of life between groups.

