### Sample Size

The primary outcome of this study is the change in cognitive function as measured using the Beijing version of the Montreal Cognitive Assessment (MoCA). We prespecified a standardized between‑group effect size of *d*=0.40 on the MoCA at 8 weeks. This assumption is supported by a recent meta‑analysis of acupuncture for PSCI showing a pooled mean difference (MD) of 3.30 points (95% CI 2.19-4.40) versus control [36,37]. Using representative poststroke variability (MoCA score mean 21.1, SD 7.5), an MD of 3.30 corresponds to a standardized effect of approximately 0.44; thus *d*=0.40 is conservative. Therefore, the trial is powered on MoCA as the primary cognitive end point.

Using G Power (version 3.2.7) with a 2-tailed test, α set at.05 (type I error), and power (1 – β) at 0.80 (type II error β=.20), the minimum required sample size was calculated to be 44 participants (22 per group) [38]. To account for an anticipated 20% dropout or loss to follow-up rate, the total sample size was increased to 54 participants, with 27 participants allocated to each group.

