### fMRI Statistical Analysis

After preprocessing, statistical analyses will be conducted with *P*<.05 as the significance threshold applying false discovery rate correction for multiple comparisons. The analysis will include the following:

DMN extraction: random 2-sample *t* tests will compare extracted DMN data between groups, with *P*<.05 considered statistically significant.Functional connectivity of the DMN: the posterior cingulate cortex, medial prefrontal cortex, and medial temporal lobe were defined as regions of interest (ROIs). Resting-state functional connections between ROIs will be calculated, and the time correlation coefficient will be obtained for the 2–independent sample *t* test.Structural connectivity of the DMN: fiber bundles between ROIs will be extracted from DTI data. The average fiber bundle length (mL), average diffusion rate (MD), and mean fractional anisotropy (mFA) will be calculated for each group and compared using 2-sample *t* tests.Correlation analysis: using correlation tests, MoCA, MMSE, MBI, and Medical Outcomes Study 36-Item Short-Form Health Survey scores; *r* values; and mL, mFA, and MD values will undergo statistical analysis. The Pearson correlation coefficient (*r*) will be obtained for the *t* test.

Multiple linear regression models will be used to examine associations between groups (acupuncture vs sham acupuncture) and posttreatment cognitive outcomes (MoCA and MMSE), adjusting for baseline covariates. Logistic regression will analyze dichotomized outcomes, and interaction terms will test moderating effects of demographic and clinical variables.

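### MoCA is given an unadjusted t test of unclear form in one section and a baseline-adjusted regression in another, with neither named primary; naming one baseline-adjusted week-8 model gains modest power at no data cost

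*Protocol article*

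**What the plan says.** The section General Data and Efficacy Indicator Statistical Analysis splits all analyses into efficacy and fMRI. It places cognition in the first group, to be compared between arms by two-tailed independent-sample t "tests or chi-square tests will be used to assess pre- and posttreatment differences in overall cognitive function". No adjustment is mentioned, and the phrase fits either a comparison of week-8 scores or a comparison of changes.

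The section fMRI Statistical Analysis ends with a second between-group analysis of the same outcome: multiple linear regression of "posttreatment cognitive outcomes (MoCA and MMSE), adjusting for baseline covariates". The covariates are not listed. The same paragraph adds logistic regression of dichotomised outcomes, with no cut-off given.

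The endpoint itself is settled. Primary Outcomes states: "The MoCA will serve as the primary outcome measure for statistical inference". Sample Size sizes the trial on a standardised effect of "0.40 on the MoCA at 8 weeks", although it also says: "The primary outcome of this study is the change in cognitive function". No section says which analysis decides the trial. The multiplicity correction in Primary Outcomes is announced for secondary outcomes only.

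**The concern.** Two matters are at stake. The first is precision. Every participant has a baseline MoCA (Table 1), and a model that adjusts for it is at least as efficient as either form of t test, apart from one degree of freedom. In a trial this small the difference is worth having, yet the efficacy section names the less efficient test.

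The second is error control. With two differently built tests on one primary endpoint and no stated order, nothing in the article prevents the deciding test from being picked after the results are known. The nominal 5% is then not assured.

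**Working it through.** **Inputs from Sample Size:** two-sided 5%, target power 80%, d=0.40 at week 8, variability taken from "MoCA score mean 21.1, SD 7.5", 22 per arm evaluable, 27 per arm randomised. **Assumed:** the correlation r between baseline and week-8 MoCA, which the article does not give. It is varied below. Scores are taken as normal with equal variance at both visits.

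**The plan's own figure.** For an unadjusted two-sample comparison, n per arm = 2(1.96+0.842)²/0.40² = 2×7.85/0.16 ≈ 98. The noncentral t solution is 99.08, so 100 per arm. The stated 22 per arm is not reproduced. That is a separate fault, and it sets the low power level of everything below.

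**Variance of the treatment estimate, relative to the week-8 t test:**
- week-8 t test: 1
- change-score t test: 2(1−r), which is 1.00, 0.80, 0.60 at r=0.5, 0.6, 0.7
- model adjusted for baseline MoCA: 1−r², which is 0.75, 0.64, 0.51

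The adjusted model's variance relative to the change score is (1−r²)/[2(1−r)] = (1+r)/2, which is 0.75, 0.80, 0.85.

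**Power.** The noncentrality is 0.40×√(22/2)/√(variance factor) = 1.327/√(variance factor), with 42 degrees of freedom for the t tests and 41 for the adjusted model. At r=0.7, for example, it is 1.327/√0.51 = 1.858 adjusted and 1.327/√0.60 = 1.713 for change.

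| Power, d=0.40 | r=0.3 | r=0.5 | r=0.6 | r=0.7 |
|---|---|---|---|---|
| Week-8 t test, 22 per arm | 25.4% | 25.4% | 25.4% | 25.4% |
| Change-score t test, 22 per arm | 19.5% | 25.4% | 30.5% | 38.7% |
| Adjusted for baseline, 22 per arm | 27.4% | 32.2% | 36.7% | 44.2% |
| Adjusted for baseline, 27 per arm | 32.7% | 38.4% | 43.8% | 52.4% |

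At 22 per arm and r=0.5 to 0.7, the gain over the week-8 t test is 32.2−25.4 = 6.8 to 44.2−25.4 = 18.8 points. Over the change-score t test it is 6.8 falling to 44.2−38.7 = 5.5 points. The adjusted model would reach 80% only at r of about 0.89 (22 per arm) or 0.86 (27 per arm).

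**Type I error if success could be claimed on any candidate test.** Null simulation, 100,000 trials per setting, 22 per arm, adjusted model with baseline MoCA as the only covariate:

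| Candidates | r=0.5 | r=0.6 | r=0.7 | r=0.8 |
|---|---|---|---|---|
| Week-8 t test or adjusted model | 7.2% | 7.9% | 8.2% | 8.7% |
| Change-score t test or adjusted model | 7.2% | 7.4% | 6.7% | 6.4% |
| Any of the three | 9.4% | 10.1% | 10.0% | 10.1% |
| Adjusted model alone | 4.9% | 5.2% | 4.9% | 4.9% |

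Results at 27 per arm are nearly the same (any of three: 9.6% to 10.2%).

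**The case against.** A fair defence runs as follows. The article condenses a fuller protocol, and an analysis plan that is not shown may rank the analyses and list the covariates. The t test stands under the efficacy heading, while the regression is described as examining associations, next to logistic and interaction models. So it is natural to take the t test as primary and the regression as supporting. Sample Size calls the primary outcome a change, which favours the change-score form, and a change score does use each patient's baseline.

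Much of this stands, and it rules out several stronger readings:

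- A reader might infer that the plan ignores baseline MoCA or throws its precision away. That is true only of the week-8 t test. The change score uses baseline, and an adjusted model is already planned.
- A reader might infer that the type I error doubles. That needs a rule of success on any of three tests. The article states no such rule, and the count of three treats one loosely worded t test as two.
- A reader might see a conflict of target between change and post-treatment score. Under randomisation all three analyses estimate the same mean difference at week 8.
- A reader might infer that baseline scores will be tested between arms. The wording allows this but does not say it, and nothing here depends on it.

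The missing covariate list can be left to an analysis plan, so it is not counted in the size above. The correlation is also uncertain: eligibility truncates baseline scores (MoCA below 26, with MMSE floors), which could lower r and shrink the gain.

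What the defence does not remove is that the article itself puts two models on its one primary endpoint without an order. The test in its efficacy section is also the less efficient one on either reading over the range examined.

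**Conclusion.** The point holds as a defect of specification with a modest gain in power on offer. With r assumed at 0.5 to 0.7, 22 per arm and d=0.40, adjustment for baseline MoCA raises power to 32% to 44%, from 25% (week-8 t test) or 25% to 39% (change-score t test). At r=0.3 the gain over the week-8 t test is only 2 points (27.4% against 25.4%).

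The risk to type I error is conditional on a choice of test that follows the data. It is then about 7% to 9% for the week-8 t test and the adjusted regression (r=0.5 to 0.8), and up to about 10% if the form of the t test is open too. One model named in advance keeps it at 5%.

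It would be wrong to conclude that adjustment rescues the trial's power. The stated 80% does not follow from d=0.40 with 22 per arm under any of the three tests at these correlations, and the sample size needs its own correction.

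**What to change.** In General Data and Efficacy Indicator Statistical Analysis, name one primary analysis: a linear model of week-8 MoCA on randomised group with baseline MoCA as covariate, tested two-sided at 5%. Report the adjusted mean difference with its 95% confidence interval. Include all randomised patients, using the multiple imputation already planned in Data Management. Any further covariate should be fixed in advance, with none left optional.

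Use the same form for MMSE, modified Barthel index and SF-36. Move the regression text out of fMRI Statistical Analysis, and label the unadjusted t tests and the logistic models as supportive.

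No new data are needed, since Table 1 already schedules MoCA at baseline and week 8. The cost is an analysis-plan amendment by the route in Ethical Considerations: ethics committee approval before implementation, notice to the registries and other parties, and an entry in the amendment log. The Results section reports nobody enrolled as of August 2025, so the change can precede the first patient.

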### fMRI Preprocessing

fMRI data will be preprocessed using the DPABI toolbox a widely used open-source platform for resting-state fMRI analysis that integrates functions such as slice timing correction, head motion realignment, normalization to Montreal Neurological Institute space, spatial smoothing, and nuisance signal regression. DPABI is based on SPM12 (Wellcome Department of Imaging Neuroscience at University College London) and MATLAB (R2023a; MathWorks). Functional connectivity and amplitude of low-frequency fluctuation analyses will be conducted in this study [44].

### fMRI Statistical Analysis

After preprocessing, statistical analyses will be conducted with *P*<.05 as the significance threshold applying false discovery rate correction for multiple comparisons. The analysis will include the following:

DMN extraction: random 2-sample *t* tests will compare extracted DMN data between groups, with *P*<.05 considered statistically significant.Functional connectivity of the DMN: the posterior cingulate cortex, medial prefrontal cortex, and medial temporal lobe were defined as regions of interest (ROIs). Resting-state functional connections between ROIs will be calculated, and the time correlation coefficient will be obtained for the 2–independent sample *t* test.Structural connectivity of the DMN: fiber bundles between ROIs will be extracted from DTI data. The average fiber bundle length (mL), average diffusion rate (MD), and mean fractional anisotropy (mFA) will be calculated for each group and compared using 2-sample *t* tests.Correlation analysis: using correlation tests, MoCA, MMSE, MBI, and Medical Outcomes Study 36-Item Short-Form Health Survey scores; *r* values; and mL, mFA, and MD values will undergo statistical analysis. The Pearson correlation coefficient (*r*) will be obtained for the *t* test.

Multiple linear regression models will be used to examine associations between groups (acupuncture vs sham acupuncture) and posttreatment cognitive outcomes (MoCA and MMSE), adjusting for baseline covariates. Logistic regression will analyze dichotomized outcomes, and interaction terms will test moderating effects of demographic and clinical variables.

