### Objectives

The primary objective is to test the hypothesis that acupuncture, compared with conventional treatment, will lead to significant improvements in poststroke cognitive function as measured using standardized neuropsychological assessments. A secondary hypothesis is that acupuncture will modulate the functional connectivity within the DMN as detected by resting-state fMRI and that changes in DMN connectivity will correlate with improvements in cognitive performance.

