**Brand New Insights**

A suite of analyses, including independent component analysis, functional connectivity analysis, and DTI analysis, will be conducted before and after the intervention to assess changes in activation patterns, functional connectivity, and structural connectivity within brain regions associated with the DMN. Correlation analyses between changes in DMN and cognitive function will be conducted to elucidate the neuroimaging correlates of the structural and functional changes within the DMN.

Crucially, all participants will receive standardized cognitive rehabilitation as part of routine clinical treatment throughout the trial, with both the acupuncture treatment group and the sham acupuncture group undergoing the same treatment regimen. This design intentionally sets cognitive training as a constant therapeutic background to isolate the specific effects of acupuncture from nonspecific placebo responses. Therefore, the observed differences between groups will solely represent the contribution of acupuncture points to neuropsychology rather than absolute treatment outcomes. This method rigorously controls cognitive training variables, precisely quantifies the incremental benefits of acupuncture based on evidence-based rehabilitation, and simulates real-world practice to demonstrate the clinical relevance of acupuncture as an adjunctive treatment. Consequently, effect sizes should be interpreted as the added value of acupuncture to a standard cognitive program, with the differences controlled via sham stimulation directly attributable to the specific neural stimulation mechanisms of acupoints.

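### The DMN-cognition correlation that tests the secondary hypothesis is specified without adjustment for residual head motion, which could produce or distort it

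*Protocol article*

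**What the plan says.** The Objectives section of the protocol article states, as part of the secondary hypothesis, that "changes in DMN connectivity will correlate with improvements in cognitive performance". The Discussion (Brand New Insights) repeats the intention: "Correlation analyses between changes in DMN and cognitive function will be conducted".

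The fMRI Statistical Analysis section then names the tests:

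- For DMN extraction, "random 2-sample *t* tests will compare extracted DMN data between groups".
- For functional connectivity between the regions of interest (ROIs), "Resting-state functional connections between ROIs will be calculated, and the time correlation coefficient will be obtained" and compared by an independent-samples t test.
- For the link with cognition and function, "The Pearson correlation coefficient (*r*) will be obtained for the *t* test".

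No covariate is attached to any of these. The same section does use an adjusted model, but for "posttreatment cognitive outcomes (MoCA and MMSE), adjusting for baseline covariates".

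Motion appears in fMRI Preprocessing, where the toolbox functions listed are "slice timing correction, head motion realignment, normalization to Montreal Neurological Institute space, spatial smoothing, and nuisance signal regression". These steps act on each scan separately. Multiplicity in the imaging analyses is handled by FDR correction.

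**The concern.** Randomization supports a comparison between arms. It does not support a correlation between two changes measured in the same patients, because nobody is randomized to a change in connectivity. Anything that moves with both changes can produce the correlation. Head motion in the scanner is a natural candidate in this trial: the patients are cognitively impaired after stroke, and the resting scan lasts about 8 minutes. If change in motion is related to change in cognition, and some effect of motion on the ROI correlations survives preprocessing, the two changes share a motion component even when the network itself plays no part.

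This correlation is what the article would rely on to explain how acupuncture works and to propose imaging markers. A motion artefact could be reported as a neural mechanism. It could also hide a real link. FDR correction controls the number of false discoveries among many valid tests; it does not repair a test whose null distribution is shifted by a confounder.

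**Working it through.** The plan gives no power, effect size or expected correlation for the imaging analyses, so there is no figure of its own to reproduce. The check asks how a plain Pearson test behaves when motion is the only thing that connectivity and cognition share.

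**Inputs**

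- N = 44 (evaluable) and N = 54 (randomized), from Sample Size.
- Two-sided level 0.05 ("with the significance level set at *P*<.05", General Data and Efficacy Indicator Statistical Analysis; the imaging section uses the same threshold).
- a = correlation of residual motion change with connectivity change; b = correlation of motion change with cognitive change. The documents give neither. Both are assumed to lie between 0.2 and 0.5 in absolute value, with a meaning what is left after nuisance regression.
- True correlation between connectivity and cognition, given motion: 0.

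**Step 1: induced correlation.** With no true link, ρ = a × b. This gives 0.2 × 0.2 = 0.04 at the low end and 0.5 × 0.5 = 0.25 at the high end.

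**Step 2: chance of a significant result.** By Fisher's z, with m = atanh(ρ) × √(N − 3), the rejection probability is Φ(m − 1.96) + Φ(−m − 1.96). For ρ = 0.09 and N = 44: m = 0.0902 × √41 = 0.578, giving 8.9%. For ρ = 0.25 and N = 54: m = 0.2554 × √51 = 1.824, giving 44.6%.

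**Step 3: simulation** (40,000 replicates per row and N), comparing the Pearson test with a partial correlation given motion:

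| Assumed a, b (absolute) | Induced ρ (absolute) | Pearson, N = 44 | Pearson, N = 54 | Partial, either N |
|---|---|---|---|---|
| 0, 0 | 0 | 5.1% | 5.2% | about 5% |
| 0.2, 0.2 | 0.04 | 5.9% | 5.8% | about 5% |
| 0.3, 0.3 | 0.09 | 9.1% | 10.1% | about 5% |
| 0.4, 0.3 | 0.12 | 12.2% | 14.1% | about 5% |
| 0.4, 0.4 | 0.16 | 18.2% | 21.5% | about 5% |
| 0.5, 0.5 | 0.25 | 37.5% | 45.1% | about 5% |

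The simulation and the formula agree to within about half a percentage point. From ρ = 0.09 upwards the error rate is higher at N = 54 than at N = 44, so more patients do not cure it.

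**Step 4: direction.** The induced correlation takes the sign of a × b. It is positive, as hypothesized, only if motion relates to connectivity and cognition in the same direction. With opposite signs it is negative and would work against a true positive link.

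**Step 5: effect of FDR.** The rates above are per test, before correction. As an illustration, assume a family of six tests (three ROI pairs by two cognitive scales). The strictest Benjamini-Hochberg threshold is 0.05 / 6 = 0.0083. Replacing 1.96 by 2.638 in Step 2 gives about 1.1% at ρ = 0.04 and about 16% (N = 44) to 21% (N = 54) at ρ = 0.25, against a nominal 0.83%. FDR lowers the absolute rate, but the excess over nominal remains.

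**The case against.** The strongest reply is that this is a condensed article that does address motion. Realignment and nuisance regression are named, the list of toolbox functions is open-ended, and a scan-exclusion limit or choice of nuisance regressors belongs in a fuller imaging plan that is not shown. Most of that stands. A reader might infer that the plan ignores head motion, or that a missing exclusion limit is an error. The documents support neither: only residual motion is in question, and silence on an exclusion limit is not a decision against one. The reply does not cover the group-level test, because the article states that test and leaves it unadjusted in the same section where it adjusts the cognitive outcomes.

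A second reply is that the size is conjecture. That is also fair. No motion correlation is given, how much nuisance regression leaves behind cannot be judged from the text, and at 0.2 for both correlations the error rate is practically nominal.

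A third concerns the arms. A reader might infer that the between-arm connectivity comparison is biased as well. Randomization balances baseline motion in expectation, and nothing in the documents shows that treatment changes motion. If it did, follow-up motion would be a post-randomization variable, and adjusting for it, or excluding scans because of it, could introduce a bias of its own. This objection succeeds against making motion adjustment the main between-arm analysis.

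**Conclusion.** The point holds for the DMN-cognition correlation. The plan fixes an unadjusted Pearson test for an across-patient association, and a better test is available from output that realignment already produces. The false-positive rate per test before FDR lies between about 6% and about 37-45% at 44 to 54 patients if residual motion correlates 0.2 to 0.5 with each variable; with motion partialled out it is about 5%. Those correlations are assumptions, and the simulation takes motion as measured without error and linearly related to both variables. A summary such as mean displacement would remove less than all of the bias in practice.

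It would be too strong to say that motion will falsely confirm the secondary hypothesis: the bias may be negligible, and it may run against the predicted sign. The primary MoCA comparison is not affected. For the between-arm connectivity tests, the documents support a sensitivity analysis and nothing more.

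**What to change.** In fMRI Statistical Analysis:

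1. Replace the Pearson DMN-cognition correlation with a partial correlation between change in connectivity and change in cognitive score, adjusting for change in mean framewise displacement. Derive displacement from the realignment parameters, and report the unadjusted correlation beside it.
2. Keep the unadjusted between-arm connectivity comparison as the main one. Add a motion-adjusted version labelled as a sensitivity analysis, noting that follow-up motion is measured after randomization.

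The cost is one degree of freedom and a little extra analysis on existing output. The Results section reports no participants enrolled as of August 2025, and Ethical Considerations sets out a route for changes to the analysis plan. If that status still holds, the change can be fixed before any data are seen.
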